## 9 STATISTICAL ANALYSIS

### 9.1 Calculation of the sample size

This study has mainly a pragmatic exploratory orientation. It aims to try to detect differences in performance between dialyzers tested whose importance is clinically relevant. To do this, it was considered that, for the measured variables, a Cohen effect size of about 0.6 in two-to-two comparisons would meet this criterion of relevance. Under these conditions, in a bilateral situation and setting a 5% alpha risk and a 20% beta risk, a minimum of 32 patients is required.

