#### General remark

The design of this study involves the comparison of 4 dialyzers for a same patient over 4 weeks. Each week begins with the use of one studied dialyzer over 2 sessions, the second session serving as a reference. Then, the third session of the week is performed with the usual dialyzer. On this basis, the participating nephrologists have considered that any risk of persistent effect (carry-over) could be excluded and that the duration of the study was short enough to rule out a period effect related to a change in the subject's clinical status (no effect period). In addition, a randomization of the Latin square type was not considered possible for practical organization reasons at each center level.

As a result, a random order of dialyzer use was decided once (random switching of 4 elements) and this order will be applied for all patients of a same center: all patients in a given center will follow the scheme allocated to this center.

The sequence of dialyzers use will be randomly assigned: per center, device  $\times$  week allocation scheme will be generated by random permutation of a block of 4 (computer generation).

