### 9.2 Principle of the analyzes

The included population will be described in terms of demographic and medical inclusion data.

Two populations of analysis are planned: the global population including all the patients with at least one dialyzer tested and the per-protocol population (PP) including all the subjects having tested the 4 dialyzers.

The main analyzes will be conducted on the PP population and additional sensitivity analyzes on the overall population.

The main analyzes will use a univariate generalized linear model integrating the variable tested as a dependent variable and the standard hemodialysis factor (2 levels: conventional HD or HDF), the dialyzer factor (4 levels) and the center factor (4 levels) as fixed factors. A full factorial model will be applied. Two-to-two comparisons will then be conducted by adjusting the alpha risk according to the Bonferonni method.

All analyses will be carried out with Statistical Package for Social Sciences version 18.0 (IBM Inc, USA).

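### The minimum of 32 patients in section 9.1 does not follow from the effect size, alpha and beta stated there: an input is wrong or has been left out

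*Protocol*

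**What the plan says.** Protocol section 9.1 sizes the trial on pairwise contrasts between dialyzers. It holds that "a Cohen effect size of about 0.6 in two-to-two comparisons would meet this criterion of relevance". The test is two-sided ("in a bilateral situation") and the result is stated as "setting a 5% alpha risk and a 20% beta risk, a minimum of 32 patients is required".

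The general remark that follows describes a within-patient design: "The design of this study involves the comparison of 4 dialyzers for a same patient over 4 weeks". Section 9.2 makes the per-protocol population (patients who tested all four dialyzers) the main one. It adds: "Two-to-two comparisons will then be conducted by adjusting the alpha risk according to the Bonferonni method".

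Section 9.1 does not say which standard deviation standardises the 0.6. It mentions no within-patient correlation, no dropout allowance and no alpha other than 5%.

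**The concern.** Section 9.1 prints what looks like a full set of inputs and a result said to follow from them, so the result can be checked, and it does not come out. This is a figure the protocol states, not a detail that it leaves to a statistical analysis plan.

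It is also the only power statement in the protocol. A reader cannot tell what power 32 patients provide for the comparison the trial is sized on, because that depends on the basis of the 0.6 and on the per-comparison alpha. Nor can a reader judge what it means if fewer than 32 patients complete all four dialyzers.

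**Working it through.** **Inputs (Protocol 9.1):** effect size d = 0.6, two-sided alpha 0.05, power 0.80 (beta 20%), stated n = 32. The design is within-patient (general remark after 9.1). Section 9.2 applies Bonferroni to the pairwise comparisons, and four dialyzers form 4 × 3 / 2 = 6 pairs.

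**Step 1: paired comparison, stated inputs.** Take 0.6 as the mean difference divided by the SD of the within-patient difference. Power is the probability that a noncentral t with n − 1 degrees of freedom and noncentrality 0.6√n exceeds the critical value in absolute size.
- Normal approximation: n = (1.960 + 0.842)² / 0.6² = 21.8, so 22.
- Exact t: n = 23 gives 78.5% and n = 24 gives 80.4%, so 24.
- At n = 32: noncentrality 0.6 × √32 = 3.39, critical value 2.04, power 90.8%.

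**Step 2: unpaired comparison, stated inputs.** Section 9.2 lists technique, dialyzer and center as factors and names no patient term, so this reading is shown as well. Noncentrality is 0.6√(n/2) with 2n − 2 degrees of freedom.
- n = 44 per group gives 79.5% and n = 45 gives 80.4%, so 45 per group (normal approximation 44).
- 32 per group give 65.6%.

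Neither reading gives 32. The gap is too wide for rounding or for the choice between t and normal. The looseness of "a Cohen effect size of about 0.6 in two-to-two comparisons" does not close it either: 0.55 needs 28 patients, and a paired requirement of 32 at 80% power corresponds to an effect of 0.51.

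**Step 3: what would give 32.** Each route needs an input that 9.1 does not print.

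| Route | Result |
|---|---|
| Paired, beta 10% instead of 20% | n = 31 gives 89.8%, n = 32 gives 90.8%: 32 |
| Paired, alpha 0.05/3 instead of 0.05 | n = 31 gives 78.4%, n = 32 gives 80.0%: 32 |
| 0.6 on the between-patient SD, within-patient correlation ρ | effect on the difference = 0.6/√(2(1 − ρ)); ρ = 0.31 gives 0.511 and 79.9% power at n = 32 |
| 24 inflated for 25% dropout | 24/(1 − 0.25) = 32 |

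The first two contradict the printed beta or alpha. An alpha of 0.05/3 would also imply three comparisons, where four dialyzers form six pairs. The last two leave the printed alpha, beta and effect size unchanged and only add an unstated input.

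**Step 4: power for the planned comparisons.** Keep 0.6 on the SD of the within-patient difference (an assumption) and use the six-pair Bonferroni alpha, 0.05/6 = 0.0083.
- 24 complete patients: 53%.
- 32 complete patients: 71%.
- n = 37 gives 79.8% and n = 38 gives 81.2%, so 80% needs 38.

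**The case against.** A reader might infer that the alpha, the beta or the 32 must be wrong. The documents do not support that. Step 3 shows two routes to 32 with all three unchanged: a between-patient SD with a correlation near 0.31, and 25% dropout on 24. The protocol states neither. However, it does not name the SD, and a main analysis restricted to patients who tested all four dialyzers would make a dropout allowance natural. What is shown is that the figure cannot be reproduced, not that any particular number is false.

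A reader might also infer that the trial is comfortably oversized, since 32 exceeds 24. That holds only for a single paired comparison at an unadjusted 5%. Section 9.2 plans adjusted comparisons, and there 32 falls short of 80% on the same effect scale. For the same reason it would mislead to print 91% alone, or to treat 24 complete patients as sufficient.

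The opposite inference, that power is only 66%, is not established either. It requires an unpaired comparison, and the design tests every patient on all four dialyzers.

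The remaining defence is that the study calls itself mainly exploratory, and that it sets one standardised effect for all measured variables. This lowers the stakes. It does not repair a formal minimum that is presented as the result of stated risks.

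**Conclusion.** The point stands as a failure to reproduce. At the inputs printed in 9.1 the requirement is 24 patients (paired) or 45 per group (unpaired), against 32 stated. The power at 32 is 91% (paired) or 66% (32 per group, unpaired), against 80% stated. A stated input is wrong or an input is missing, and the protocol does not allow a reader to say which.

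The figures rest on t-tests with normal errors. The paired ones further assume that 0.6 is on the SD of the within-patient difference and that all counted patients are complete. The 71% and the 38 also assume that the Bonferroni family is the six dialyzer pairs, with all 32 patients pooled across techniques.

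The point should be corrected, but it gives no reason to change the number of patients.

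**What to change.** Keep 32 patients and rewrite the last sentence of Protocol 9.1 so that it states:
- the test used for the calculation;
- the SD that standardises the 0.6 (within-patient difference or between-patient), with the assumed correlation if it is the latter;
- any dropout allowance;
- the per-comparison alpha and the beta that gave 32.

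Then add the power for the analysis in 9.2. If the sponsor confirms that 0.6 is on the SD of the within-patient difference, suitable wording would be: *With 32 complete patients, a standardised within-patient difference of 0.6 is detected with about 91% power at an unadjusted two-sided 5% alpha, and with about 71% power at the Bonferroni alpha of 0.05/6 for six pairwise comparisons, for which 80% would require 38 patients.* If the basis was different, the powers should be recomputed on that basis and not copied from here.

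The cost is a few sentences, with no extra patients, visits or assays. The downside is that the stated power becomes less favourable for the Bonferroni-adjusted comparisons.

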#### General remark

The design of this study involves the comparison of 4 dialyzers for a same patient over 4 weeks. Each week begins with the use of one studied dialyzer over 2 sessions, the second session serving as a reference. Then, the third session of the week is performed with the usual dialyzer. On this basis, the participating nephrologists have considered that any risk of persistent effect (carry-over) could be excluded and that the duration of the study was short enough to rule out a period effect related to a change in the subject's clinical status (no effect period). In addition, a randomization of the Latin square type was not considered possible for practical organization reasons at each center level.

As a result, a random order of dialyzer use was decided once (random switching of 4 elements) and this order will be applied for all patients of a same center: all patients in a given center will follow the scheme allocated to this center.

The sequence of dialyzers use will be randomly assigned: per center, device  $\times$  week allocation scheme will be generated by random permutation of a block of 4 (computer generation).

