## 7 METHODOLOGY

### 7.1 Study design, dialyzers and dialysis conditions

This study is a prospective multicenter randomized comparative cross-over trial.

Four different dialysis facilities (AURA Paris, Yvetot clinic, AIDER clinic and Toulouse university hospital center) will be involved in the study.

Eligible patients will be assigned to receive either post-dilution HDF (first two centers) or conventional high-flux HD (last two centers) for 4 weeks. During this period, all patients will be sequentially dialyzed with 4 different dialyzers (one/week, the two first sessions of the week; the

last session of the week being performed with the patient's own dialyzer and used as a wash out session): Leoced 21HX, Polypure 22S+, Rexsys 27H and VIE-21A.

The sequence of dialyzers use will be randomly assigned: per center, device × week allocation scheme will be generated by random permutation of a block of 4 (computer generation). All patients in a given center will follow the scheme allocated to this center. The randomization sequence will be centralized and computed by the statistician.

No run-in period before entering in the active study phase will be performed

Dialysis sessions will be conducted according to usual procedures of the center, with increased monitoring and control of the patients treated with the tested hemodialyzers.

Patients will be treated in HD or post-dilution HDF, according to the usual conditions, specific to each patient. The frequency of dialysis (3 sessions per week), the duration of dialysis (3- 4h), the blood flow of the extracorporeal blood circuit ( $\geq 300$  mL/min), the type (dialysate bicarbonate or other) and the dialysate flow (700 mL/min) will remain unchanged or will be documented in case of modification.

In case of need for adjustment, or changes in prescription of the medication, these changes will be documented. The modifications will respect recommendations.

[figure not shown]

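### Dialyzer is fully aliased with week inside each center and partly confounded with it overall; a Latin square with one row per center would prevent this

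*Protocol*

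**What the plan says.** Protocol 7.1 describes "Four different dialysis facilities", with patients receiving "either post-dilution HDF (first two centers) or conventional high-flux HD (last two centers) for 4 weeks". Each patient uses all four dialyzers, one per week. The order is set by center: the device-by-week scheme is "generated by random permutation of a block of 4 (computer generation"), and "All patients in a given center will follow the scheme allocated to this center". Nothing in 7.1 or 9.1 links one center's order to another's.

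The General remark in 9.1 gives the reasoning. Carry-over is excluded because the week's third session uses the patient's usual dialyzer. A period effect arising from a change in clinical status is excluded because the study is short. A Latin square is refused: "a randomization of the Latin square type was not considered possible for practical organization reasons at each center level". The remark then states that "a random order of dialyzer use was decided once (random switching of 4 elements") and that this order applies to all patients of one center.

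The main model in 9.2 contains modality, dialyzer and center as fixed factors in full factorial form. It has no term for week or sequence.

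**The concern.** Inside a center every patient uses the same dialyzer in the same study week, so a dialyzer difference there is also a week difference. Only differences between the four center orders can separate the two, and those orders are left to four unconstrained draws. The 32 patients therefore supply at most four distinct sequences, too few for chance to balance dialyzers over weeks.

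The exclusion of period effects covers clinical status only and rests on judgement. It does not cover staff familiarity with a new procedure, sample handling or session conditions. Protocol 7.1 itself provides for documenting changes in session settings and medication. With no week term, any such trend enters the dialyzer comparison on the primary outcome, the β2-microglobulin reduction ratio.

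The stated obstacle to a Latin square concerns organization within a center. With four centers, four dialyzers and four weeks, a square across centers fits exactly and leaves each center with a single order.

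**Working it through.** The protocol gives no figure for week balance, so there is none to reproduce. The sample size of 32 plays no part here.

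**Inputs.** From 7.1 and 9.1: 4 centers (2 HDF, 2 HD), 4 dialyzers, 4 weeks and one random order of 4 per center. I take the draws as independent, because the scheme is generated per center and no constraint is stated. I also assume equal center sizes.

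**Quantity.** For dialyzer i, the mean week is m_i = (1/4) × the sum over centers of the week in which i is used. With a linear drift of s per week and no week term, the bias for the pair i, j is s × (m_i − m_j).

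**Chance of balance.** There are 24^4 = 331,776 sets of four orders, of which 576 are Latin squares: 576 / 331,776 = 0.17%.

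**Full enumeration** (first center fixed by symmetry, 24^3 = 13,824 cases):

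| Quantity | Result |
|---|---|
| Largest gap in mean week, all four centers | median 1.25, mean 1.34 (10th to 90th percentile 0.75 to 2.0) |
| Largest gap at least 1 week | 80% of draws |
| Average gap over the six pairs | 0.73 week |
| Some dialyzer in the same week in 3 or more centers | 55.6% of draws |
| Largest gap within one modality (2 centers) | mean 1.875 weeks |
| Average pair gap within one modality | 1.03 weeks |
| Some dialyzer contrast not estimable once week is added | 7.0% of draws |

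Two centers of one modality avoid sharing any dialyzer-week in 9 of 24 cases, so they share at least one in 1 − 9/24 = 62.5%.

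**Size of bias.** The documents give no drift, so s is an assumption shown over a range:

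| Assumed s (SD per week) | Worst pair, median draw (1.25 × s) | Average pair (0.73 × s) |
|---|---|---|
| 0.05 | 0.06 SD | 0.04 SD |
| 0.10 | 0.125 SD | 0.07 SD |
| 0.20 | 0.25 SD | 0.15 SD |

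The planning effect in 9.1 is about 0.6.

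**Can week simply be added to the stated model?** No. The center-by-dialyzer full factorial has 4 × 4 = 16 cells, and each cell occurs in exactly one week. Its rank is 16 with or without week, so week cannot be separated from that interaction. With center, dialyzer and week as main effects only, the efficiency of the dialyzer contrasts averages 0.65 over independent draws, against 1.00 for a Latin square.

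**The alternative.** Take orders ABCD and DCBA in one modality, BDAC and CADB in the other. Over these four orders A falls in weeks 1, 4, 3, 2; B in 2, 3, 1, 4; C in 3, 2, 4, 1; D in 4, 1, 2, 3. Each dialyzer occurs once in each week, so m_i = 2.5 throughout. Within the first modality A averages (1 + 4)/2 = 2.5 and B (2 + 3)/2 = 2.5; C and D, and all four in the second modality, also average 2.5. Each dialyzer directly follows each other dialyzer once.

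The mirror pairing matters. If Williams rows go to centers at random, the largest within-modality gap is 0 in one third of assignments and 2.0 weeks in two thirds, an average of (2/3) × 2.0 = 1.33.

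**The case against.** The trial calls itself mainly exploratory, its orders are randomized, and it gives reasons for dismissing carry-over and period effects. The primary outcome is a ratio of two samples from one session, so a proportional assay shift cancels if both are assayed together, and β2-microglobulin is measured centrally. Session settings are meant to stay unchanged and are recorded weekly. Recruitment runs for 6 months (7.2). If patients in a center start on different dates, calendar effects are only loosely tied to study week. The 1.25-week figure describes the worst pair; the average pair gap is 0.73 week.

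Most of this stands. It lowers the plausible drift and therefore the severity. It does not give a reason for leaving the orders unlinked, and neither recording settings nor central assay removes a trend tied to a patient's study week.

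Two stronger readings are tempting. A reader might infer that dialyzer and week are inseparable throughout the trial. That is true within a center, but across centers it would require all four orders to coincide. A reader might also take "a random order of dialyzer use was decided once (random switching of 4 elements") to mean one order for the whole trial. The same sentence applies that order to the patients of one center, and both 7.1 and the next paragraph of 9.1 say the scheme is drawn per center. Once per center is the natural meaning; the wording needs only clarification.

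**Conclusion.** The point holds as an avoidable partial confounding that should be fixed. Dialyzer and week are fully aliased within each center and partly confounded overall. In the median draw the worst-placed pair differs by 1.25 weeks in mean position. For an assumed drift of 0.05 to 0.2 SD per week that is a bias of about 0.06 to 0.25 SD. Comparisons within HD or HDF rest on two centers each and are more exposed, with a mean largest gap of 1.9 weeks.

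These figures assume independent draws, equal center sizes and a linear drift common to the centers. The protocol neither supplies nor excludes such a drift, apart from change in clinical status. A reader might conclude that the primary comparison is invalid. The documents do not support that: no drift is shown, and the bias is zero if there is none.

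**What to change.** **Allocation (7.1 and 9.1).** Replace the unlinked permutations by the rows of one randomised 4x4 Williams square. Give one mirror-image pair to the two HDF centers and the other to the two HD centers, for example ABCD/DCBA and BDAC/CADB. Randomise letters to dialyzers, pairs to modalities and rows to centers. With roughly equal center sizes, each dialyzer is then balanced over weeks overall and has mean week 2.5 within each modality.

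**Wording (9.1).** State that the order is decided once per center.

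**Model (9.2).** Add week as a fixed effect in a model without the center-by-dialyzer interaction. With the mirror-paired square, a three-parameter week term fits fully alongside center and dialyzer. If the modality-by-dialyzer interaction is kept, the model has rank 12, where 13 is needed. Weeks 1 and 4 against 2 and 3 then coincide with one modality-by-dialyzer contrast, so use a linear week term there and acknowledge that a U-shaped pattern cannot be separated from it.

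**If orders are already drawn.** Keep them and fit the additive week model as a sensitivity analysis, after checking that all dialyzer contrasts are estimable (they are not in 7.0% of draws).

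**Cost.** A different computer draw, 3 degrees of freedom for week, and loss of the center-by-dialyzer interaction in that model. There are no extra patients or sessions, and each center still runs one order.

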### 9.2 Principle of the analyzes

The included population will be described in terms of demographic and medical inclusion data.

Two populations of analysis are planned: the global population including all the patients with at least one dialyzer tested and the per-protocol population (PP) including all the subjects having tested the 4 dialyzers.

The main analyzes will be conducted on the PP population and additional sensitivity analyzes on the overall population.

The main analyzes will use a univariate generalized linear model integrating the variable tested as a dependent variable and the standard hemodialysis factor (2 levels: conventional HD or HDF), the dialyzer factor (4 levels) and the center factor (4 levels) as fixed factors. A full factorial model will be applied. Two-to-two comparisons will then be conducted by adjusting the alpha risk according to the Bonferonni method.

All analyses will be carried out with Statistical Package for Social Sciences version 18.0 (IBM Inc, USA).

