## 1 PROJECT SUMMARY

Objectives of this prospective multicenter randomized cross-over study are to evaluate the influence of two dialysis treatments (HD vs post-dilution HDF) with four high-flux (polysulfone or polyethersulfone) dialyzers i) in the clearance evaluation for small, middle and large molecular weight substances and ii) in the modification of several biological responses including parameters of inflammation and nutrition. In addition, a comparative quantification of perdialytic albumin losses using either a partial collection of continuous spent dialysate or the total dialysate collection will be performed in a subgroup of patients. Primary outcome will be  $\beta$ 2-microglobulin removal. Secondary outcomes will be i) extraction of other uremic solutes ii) parameters of inflammation and nutrition and iii) comparative quantification of perdialytic albumin losses.

32 chronic kidney disease patients treated with extrarenal replacement therapy and issued from 4 dialysis centers will be assigned to receive either post-dilution HDF (2 first centers) or conventional high-flux HD (2 other centers) for 4 weeks. During this period, all patients will be sequentially dialyzed with 4 different dialyzers (one/week): Leoced 21HX, Polypure 22S+, Rexasys 27H and VIE-21A. The sequence of dialyzers use will be randomly assigned. All patients in a given center will follow the scheme allocated to this center.

Dialysis conditions will remain unchanged for each patient: 3 sessions/week, 3-4 hours/session, blood flow (QB) of 300-400mL/min, ultrapure bicarbonate buffered dialysate, dialysate flow (QD) in the range 500-700mL/min.

Blood samples will be drawn weekly during the midweek dialysis session before and after dialysis. Routine laboratory analyses including serum urea, creatinine and PO4 (all being evaluated pre- and post-dialysis) will be locally performed. Specific biomarkers including serum  $\beta$ 2-microglobulin, myoglobin, free light chain  $\kappa$ , Beta Trace Protein, myostatin, orosomucoid, CRP, TNF- $\alpha$ , IL-6, albumin and transthyretin will be performed on frozen samples in a central laboratory.

Results of this study should bring additional information on the performance and biocompatibility of the 4 hemodialyzers tested and help in personalizing device prescription according to dialysis treatment (HD or HDF) and patient profile.

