### 5.3 Exit criteria

- ❑ Express request of the patient
- ❑ Medical decision
- ❑ Move to another dialysis center not participating in the study
- ❑ Transplantation
- ❑ Medication without prior agreement of the physician
- ❑ Death

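### The main analysis keeps only patients who tested all four dialyzers, so valid sessions of other patients are dropped and the all-patient check is weak without a patient term

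*Protocol*

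**What the plan says.** Section 9.2 of the protocol defines two analysis sets. One is "the global population including all the patients with at least one dialyzer tested"; the other is "the per-protocol population (PP) including all the subjects having tested the 4 dialyzers". It then gives them their roles: "The main analyzes will be conducted on the PP population and additional sensitivity analyzes on the overall population". The model for the main analyses has modality, dialyzer and center as fixed factors, in full factorial form, followed by Bonferroni-adjusted pairwise comparisons. No patient factor is listed.

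Section 9.1 assumes "a Cohen effect size of about 0.6 in two-to-two comparisons", "in a bilateral situation and setting a 5% alpha risk and a 20% beta risk", and concludes that "a minimum of 32 patients is required". Section 1 plans to enrol exactly that number. Neither section gives an expected loss, an inflation factor or a replacement rule.

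Section 5.3 lists the ways out of the study. They include the patient's own request and "Medical decision".

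**The concern.** Each patient gives one sampled midweek session per dialyzer, so four in all. Under the completer rule, a patient with three good sessions and one missing dialyzer contributes nothing to the primary result. Nothing in the stated model requires four sessions per patient, so the exclusion is a choice.

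Two further points follow. First, exit by patient request or physician decision could be linked to a particular membrane; the completers would then be a selected group. Second, the all-patient run that should reveal such a problem uses a model that does not link a patient's sessions to each other, so it may not show the problem clearly. At stake are some precision in the dialyzer contrasts and the means of checking whether they depend on who completed.

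**Working it through.** **1. The plan's own figure.** The inputs are those of section 9.1: effect 0.6, two-sided 5% alpha, 80% power.
- Paired comparison, normal approximation: n = ((1.960 + 0.842)/0.6)² = 21.8, so 22. The exact paired t-test needs 24.
- Two independent groups: 44 per group (normal) or 45 (exact t).
- A paired t-test with Bonferroni for three comparisons needs exactly 32. For all six pairs it needs 34 (normal) or 38 (exact t).

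The basis of 32 is therefore unstated, but it is not shown to be wrong. On the unadjusted paired reading, 24 completers suffice and 32 − 24 = 8 patients are slack. The protocol does not present this slack as an attrition allowance.

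**2. Assumed loss.** The protocol gives no rate. Let each session be lost independently with probability p, and count a lost session as a dialyzer not tested.
- Expected completers: 32 × (1 − p)⁴.
- Expected patients with both sessions of a given pair: 32 × (1 − p)².
- Share of validly measured sessions dropped by the completer rule: 1 − (1 − p)³.

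Power is from the two-sided paired noncentral t with a standardised difference of 0.6, at the rounded n.

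| p | Completers | Power at 5% | Both sessions of a pair | Power at 5% | Valid sessions dropped |
|---|---|---|---|---|---|
| 0 | 32 | 91% | 32 | 91% | 0% |
| 3% | 28.3, so 28 | 86% | 30.1, so 30 | 89% | 9% |
| 5% | 26.1, so 26 | 84% | 28.9, so 29 | 88% | 14% |
| 10% | 21.0, so 21 | 74% | 25.9, so 26 | 84% | 27% |

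Before rounding, the gain from using all sessions is about 2, 4 and 9 percentage points.

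**3. With Bonferroni.** Four dialyzers give six pairs, so alpha is 0.05/6. Power at 32 with no loss is already 71.4%, against 90.8% unadjusted: a drop of 19.4 points that has nothing to do with attrition. Completer-only loss then takes it to 63.0%, 58.2% or 45.0%, a further 8.4, 13.2 or 26.4 points. At 3% and 5% loss the Bonferroni step is the larger one; only at the 10% assumption does attrition overtake it.

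**4. The all-patient check.** When every patient has all four sessions, a difference between two dialyzer means equals the mean within-patient difference, so stable patient characteristics cancel. Once patients are incomplete, the fixed-factor model compares dialyzer means over different people within a center, and between-patient differences enter the contrast. Sections 7.1 and 9.1 also give all patients of a center the same dialyzer order, so early exits in a center always remove the same late-scheduled dialyzers. A difference between the two analyses could then reflect a change of patients as easily as selection.

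**The case against.** The strongest reply is that completers are the safer set under the model as written. Each contributes all four dialyzers, so the contrast stays within patient. Selection would mainly limit generalisability; it would bias the β2-microglobulin contrast only if the reason for leaving were linked to device-specific removal, and no section suggests such a link. The devices are CE-marked and used in their indications, the study lasts four weeks, it is described as mainly exploratory, and an all-patient analysis is already prespecified. The PP set is also defined by dialyzers tested, not by evaluable samples, so one unusable assay does not clearly exclude a patient and the table may overstate the losses. All of this stands, and it limits the size of the point.

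A reader might infer more than the documents support in three ways:
- That the primary analysis excludes patients who tolerated a device badly. Section 5.3 has only generic exit items; tolerance-related exit is possible, not shown.
- That attrition leaves the trial underpowered. At the stated 5% alpha, the 3% and 5% cases stay above 80%. The 10% case implies that 34% of patients fail to complete within four weeks, and nothing in the protocol points to that.
- That exchanging the two populations is enough. Without a patient effect it would make the main analysis worse.

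The mixed model is no complete cure either. If exit depends on something that affects removal and is not reflected in the observed sessions, missing at random fails.

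What the reply leaves untouched is that valid sessions are dropped for no need of the model, and that the planned check is hard to interpret.

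**Conclusion.** The point holds as a modest weakness in the analysis plan. The choice of main set is fixed in the protocol itself, although a separate statistical analysis plan, not available here, may hold finer missing-data rules. Using all sessions with a patient effect would raise paired power at 5% from 86%, 84% or 74% to about 89%, 88% or 84% under assumed per-session losses of 3%, 5% or 10%. These figures rest on three assumptions: independent losses, 0.6 read on the scale of the paired difference (section 9.1 does not say), and a paired test as stand-in for the model. If nobody is lost, the two sets coincide and nothing changes. Selection by device remains a possibility only. The low power at 5%/6 exists before any patient is lost and should not be attributed to the completer rule.

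**What to change.** In section 9.2, make one joint change:
- Main set: all patients with at least one evaluable dialyzer session.
- Model: a linear mixed model with a random patient effect, valid if data are missing at random given the observed sessions.
- Sensitivity analysis: patients who tested all four dialyzers.

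Do not exchange the populations while keeping the present model.

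In section 9.1, state that 32 contains no explicit attrition allowance. If the sponsor nevertheless wants 32 completers, enrolment is 32/(1 − d), where d is the share of patients lost: 34, 36, 38 or 40 for an assumed 5%, 10%, 15% or 20%.

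The cost is a short rewrite of section 9.2 and a sentence in 9.1, with no new data. The downside is that the model itself changes and the main result then rests on the missing-at-random assumption, which the completer analysis can help to examine but cannot prove.
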